## Abstract

**Background:**

Palmoplantar pustulosis (PPP) is a rare, debilitating inflammatory skin disease involving painful pustules on the palms and soles. Janus kinase (JAK) inhibitors target pathways relevant to PPP disease biology but also confer a risk of major adverse cardiovascular events and malignancy in certain ‘at risk’ individuals; this includes those with PPP given prevalent smoking and cardiovascular risk factors in the PPP population. The feasibility of JAK inhibitor therapy for PPP requires assessment prior to a randomised controlled trial evaluation of drug efficacy and safety for this indication.

**Methods and analysis:**

The ‘Janus kinase inhibitors in palmoplantar pustulosis: a mixed-methods feasibility’ trial is an open-label, single-centre, single-arm, mixed-methods feasibility trial of JAK inhibition in PPP (REC reference: 24/NE/0147; ISRCTN61751241). Participants (n=20) will receive 8 weeks of treatment with the JAK inhibitor upadacitinib (‘Rinvoq’, 30 mg, once daily). Qualitative semistructured interviews (up to n=40) will be undertaken with trial participants, trial decliners and healthcare professionals. The primary outcome will be a composite assessment of feasibility across three domains: recruitment, adherence and acceptability, using a mixed-methods analysis approach. Secondary objectives include the identification of trial recruitment optimisation strategies, using the ‘Quintet Recruitment Intervention’, and the generation of an indication of effect size on disease severity (measured using the Palmoplantar Pustulosis Psoriasis Area and Severity Index) to inform future sample size calculations. Historic placebo control data from the Anakinra for Pustular Psoriasis: Response in a Controlled Trial (National Institute of Health and Social Care reference: 13/50/17; Research Ethics Commitee reference: 16/LO/0436) will be used as the effect size comparator. Study recruitment will be undertaken over a 24-month period, commencing in November 2024.

**Ethics and dissemination:**

This study has been approved by the Newcastle North Tyneside 2 Research Ethics Committee, 24/NE/0132. Our findings will inform the feasibility of a future adequately powered RCT evaluating the efficacy of JAK inhibitor therapy in PPP.

**Trial registration number:**

ISRCTN61751241.

STRENGTHS AND LIMITATIONS OF THIS STUDYThe Quintet Recruitment Intervention and use of historic placebo controls may generate generalisable knowledge on trial recruitment and delivery in rare disease research.The study aim is to evaluate feasibility; future work will be required to establish the clinical effectiveness of Janus kinase inhibitor therapy in palmoplantar pustulosis.This is a single-arm, single-centre study conducted in a tertiary care setting which may limit the generalisability of findings. ⁠

## Background

 Palmoplantar pustulosis (PPP) is a rare, chronic, immune-mediated skin disease, characterised by painful, intensely inflamed skin on the palms and soles, studded with sheets of pustules. The prevalence of PPP is estimated as 6.4–89.4/100 000 population, with a higher preponderance in Asia, and among females.^1^ It typically presents in middle age and is closely associated with a history of smoking.^2^

Conventional systemic and targeted biologic immunomodulatory therapies display limited efficacy in PPP, posing a significant therapeutic challenge, and there are no currently licensed treatments for PPP in the UK.^3^ Transcriptomic studies have identified strong T2-mediated and T17-mediated inflammatory signatures in the pathogenesis of PPP.^4^ The simultaneous activation of multiple immune pathways may account for the limited therapeutic efficacy of targeted biologic therapies in this condition.

Janus kinase (JAK) inhibitors are a novel class of targeted immunomodulators that are increasingly used in medical specialities, including rheumatology (eg, psoriatic arthritis), gastroenterology (eg, ulcerative colitis), and dermatology (eg, atopic eczema).^5^ JAK inhibitors exert broad immunosuppressive effects via pleiotropic inhibitory effects across several intracellular inflammatory cascades, providing a strong potential rationale for their use in PPP. Consistent with this are case reports and case series supporting their potential as a therapeutic option in PPP, with a recent critical appraisal of the literature identifying 39 cases of near/complete skin clearance following treatment with different JAK inhibitors.^6^ However, there is currently a lack of trial evidence to support this management approach in PPP.

Given the growing clinical evidence and a plausible scientific underpinning to support the use of JAK inhibitors as a treatment for PPP, further investigation in a trial setting is warranted. However, the feasibility of an adequately powered definitive randomised controlled trial (RCT) assessing the efficacy of JAK inhibitor therapy in PPP is unclear, due to several key challenges.

The first challenge relates to recent safety concerns regarding JAK inhibitor therapy following a randomised, open-label, non-inferiority, post-authorisation trial of 2911 patients with rheumatoid arthritis. This study evaluated the safety and efficacy of the JAK inhibitor tofacitinib compared with tumour necrosis factor (TNF) inhibitor therapy in patients with rheumatoid arthritis who were 50 years of age or older and had at least one additional cardiovascular risk factor.^7^ During a median follow-up of 4 years, the incidence of major adverse cardiovascular events (MACEs) was higher with combined tofacitinib (3.4%; 98 patients) than with a TNF inhibitor (2.5%; 37 patients). Non-inferiority of tofacitinib compared with TNF inhibitor therapy was not shown (HR, 1.33; 95% CI: 0.91 to 1.94), because the upper boundary of the 95% CI was more than 1.8 (the pretrial stated non-inferiority cut-off). Similarly, the incidence of cancers (excluding non-melanoma skin cancer) was higher with tofacitinib (4.2%; 122 patients) than with a TNF inhibitor (2.9%; 42 patients). Non-inferiority of tofacitinib compared with TNF inhibitor therapy was not shown (HR, 1.48; 95% CI, 1.04 to 2.09), with the upper boundary of the 95% CI more than 1.8 again.

Tofacitinib is a pan-JAK inhibitor, and it is not currently known how these safety signals relate to more selective JAK inhibitors, such as upadacitinib (a JAK-1 selective inhibitor). A recent meta-analysis found that there was no increased risk of malignancy associated with JAK inhibitor use when compared with placebo, highlighting the need for further research and long-term follow-up safety data in this area.^8^ Nonetheless, the recent safety concerns have prompted the introduction of new guidance from regulatory bodies cautioning the use of JAK inhibitors in at-risk populations (age >65 years; current or long-term former smokers; those with other cardiovascular or malignancy risk factors).^9^

These safety signals are highly relevant in the context of PPP. The prevalence estimate of smoking among the PPP population is 78.2%, and cumulative pack-year history and longer duration of smoking are associated with a greater risk of disease development.^10^ The current regulatory framework means that JAK inhibitors may be relatively contraindicated in a substantial proportion of people with PPP, and both clinicians and people with PPP may be reluctant to use JAK inhibitors in light of these potential risks. Therefore, successful participant recruitment to an RCT may thus be difficult to achieve.

This recruitment challenge is especially pertinent given PPP is a rare disease. Poor trial recruitment is a prominent issue in the study of rare diseases, leading to research failure and increased costs. Only half of publicly funded trials in the UK between 1997 and 2020 achieved their original recruitment target, and a third required an extension.^11^ Given these recruitment challenges and acceptability concerns, a feasibility assessment of the use of JAK inhibitor therapy in PPP is warranted prior to a definitive adequately powered RCT.

Poor medication adherence is also a prevalent issue in chronic diseases. It is estimated that roughly 50% of patients with a chronic disease do not take their medication as prescribed.^12^ Given the acceptability concerns highlighted, an exploration of adherence in this context is warranted, especially considering the high cost of JAK inhibitors.

An exploratory feasibility trial also provides the opportunity to explore innovative trial recruitment and efficiency strategies, such as the Quintet Recruitment Intervention (QRI).^13^ This two-phase, recruitment-focussed, quality improvement methodology has been used in at least 23 studies since 2016, ranging from surgery through to oncology, and in both feasibility and definitive trial settings. It has yet to be used in an inflammatory disease trial, or in dermatology, and PPP provides an exemplar rare disease in which to trial this approach.

Another strategy to enhance trial efficiency is the use of historic controls. Historic controls are individuals studied in a previous trial used as a comparison group in a future study that has no control group.^14^ Reusing data from the placebo arms of previous RCTs offers the potential to minimise risks, cost and inconvenience by reducing enrolment time, decreasing participant numbers, minimising potential bias due to dropout, accelerating trial completion and thus reducing time to treatment approval.^15^ Historic placebo controls have yet to be used more widely in the context of inflammatory diseases. We will pilot the use of historic controls in this setting, incorporating historic control data from the placebo group of the Anakinra for Pustular Psoriasis: Response in a Controlled Trial (APRICOT) as the comparator group. The APRICOT investigated the use of anakinra in the management of PPP against a placebo control and was conducted from 2015 to 2020.^16^ We have followed guidance from a recently published roadmap on the use of historic controls, mirroring the APRICOT processes and eligibility criteria in the proposed trial, ensuring the robustness of this approach.^17^

## Objective

The ‘Janus kinase inhibitors in palmoplantar pustulosis: a mixed-methods feasibility (JAKPPPOT)’ trial is an open-label, single-arm study which aims to determine the feasibility of JAK inhibitor therapy in PPP, via a composite, mixed-methods assessment of three domains: recruitment, adherence and acceptability. This study will provide an indication of effect size using historical control data from the APRICOT study and will identify trial optimisation strategies to bolster the recruitment in a definitive trial.^16^

## Methods

This protocol has been prepared and reported in accordance with the Standard Protocol Items: Recommendations for Interventional Trials (SPIRIT) guidance.^18^ The trial SPIRIT checklist is available (online supplemental file 1).

### Study design

JAKPPPOT is an open-label, single-arm, mixed-methods feasibility trial, conducted at St John’s Institute of Dermatology, Guy’s and St Thomas’ NHS Foundation Trust, UK (figure 1). Participants (n=20) will receive 8 weeks of treatment with the JAK inhibitor upadacitinib (‘Rinvoq’, 30 mg, once-a-day). Integrated qualitative semistructured interviews (up to n=40) will be undertaken with trial participants, trial decliners and healthcare professionals. Recruitment optimisation strategies will be identified and implemented via the QRI process incorporated into this trial. The study endpoint is 20 participants successfully recruited, or 24 months elapsing, whichever occurs first.

**Figure 1 F1:**
[figure not shown]
Overview of the JAKPPPOT study design. JAKi, Janus kinase inhibitor; JAKPPPOT, Janus kinase inhibitors in palmoplantar pustulosiAnus Kinase inhibitors in PalmoPlantar PustulOsis: a mixed-methods feasibility; PPP, palmoplantar pustulosis; QRI, Quintet Recruitment Intervention.

### Study population

The study population is adult patients (≥18 years) with a dermatologist-confirmed diagnosis of PPP requiring systemic immunomodulatory therapy. The full inclusion and exclusion criteria are listed in table 1. In line with the Medicines and Healthcare products Regulatory Agency’s (MHRA) recent advice, upadacitinib will only be used in the following cohorts if no suitable treatment alternatives are available^9^:

**Table 1 T1:** Inclusion and exclusion criteria

Inclusion criteria	Exclusion criteria
Adults (18 years and over) with a diagnosis of palmoplantar pustulosis* made by a trained dermatologist with disease of sufficient impact and severity to require systemic therapy Disease duration of ≥6 months, not responding to an adequate trial of topical therapy including very potent corticosteroids Evidence of active pustulation on palms and/or soles At least moderate disease based on a Palmoplantar Pustulosis Investigator Global Assessment Able to give written, informed consent to participate Willing and able to comply with scheduled visits, treatment plan, laboratory tests and other study procedures.	A history of malignancy of any organ system (other than treated, localised non-melanoma skin cancer), treated or untreated, within the past 5 years A history of provoked or unprovoked venous thromboembolism (deep vein thrombosis or pulmonary embolism), unless actively treated with long-term anticoagulation Previous systemic treatment with a JAK inhibitor A history of recurrent bacterial, fungal or viral infections which, in the opinion of the principal investigator, present a risk to the patient Evidence of active infection or untreated latent tuberculosis HIV positive Active or untreated Hepatitis B or C Use of therapies with potential or known efficacy in psoriasis during or within the specified timeframe before treatment initiation as listed in the washout section Moderate renal impairment (CrCl < 50 mL/min) Neutropenia (<1.5×10^9^/L) Thrombocytopenia (<150×10^9^/L) Moderate hepatic disease and/or raised hepatic transaminases (ALT/AST) > 2 x upper limit of normal at baseline. Patients who fail this screening criterion may still be considered following review by a hepatologist and confirmed expert opinion that study entry is clinically appropriate. Live vaccinations within 3 months prior to the start of study medication, and no planned live vaccinations during the trial and up to 3 months following last dose Women who are pregnant, breast feeding or of childbearing potential not on adequate contraception Male participants who are not willing to use highly effective methods of contraception when engaging in sexual activity with a female of childbearing potential Any condition where, in the opinion of the investigator, the investigational medical product would present risk to the patient. Unable to give written, informed consent. Unable to comply with the study visit schedule Known hypersensitivity to upadacitinib and/or its excipients (SmPC 6.1) Receipt of any of the following within the specified timeframe before treatment initiation (baseline, visit 1): Topical treatments likely to impact signs and symptoms of psoriasis (eg, potent/very potent corticosteroids, vitamin D analogues, calcineurin inhibitors) within 2 weeks Systemic immunosuppressants (eg, methotrexate, ciclosporin, acitretin) within 4 weeks Phototherapy (UVB TL01, UVB, PUVA, UVA1) within 4 weeks Etanercept or adalimumab within 4 weeks Other biologic therapies (infliximab, certolizumab, ustekinumab, secukinumab, ixekizumab, risankizumab, bimekizumab, brodalumab, tildrakizumab, guselkumab) within 3 months Other investigational drugs within 4 months or five half-lives (whichever is longer) Other immunosuppressant/immunomodulatory therapies including intra-articular steroids within 30 days or five half lives (whichever is longer)

* Different forms of psoriasis can co-present together (eg, chronic plaque psoriasis, acrodermatitis of Hallopeau, generalised pustular psoriasis). A concomitant diagnosis of a different type of psoriasis will not be a contraindication to eligibility.

ALT, alanine aminotransferase; AST, aspartate aminotransferase; CrCl, creatinine clearance; SmPC, summary of product characteristics.

Age 65 years or older.Patients with a history of atherosclerotic cardiovascular disease or other cardiovascular risk factors (such as past long-term smokers).Patients with malignancy risk factors (eg, current malignancy or history of malignancy).

Any decision to treat patients in these cohorts will be made following discussion with the chief investigator and will be based on individualised patient factors.

### Intervention

Participants will receive 8 weeks of treatment with upadacitinib (‘Rinvoq’, 30 mg, once daily, oral tablet). In certain patient cohorts, outlined in Section 4.4 of the summary of product characteristics, the investigational medical product (IMP) dose may be moderated to 15 mg, once daily, oral tablet. These cohorts include patients at higher risk of venous thromboembolic events, MACEs and malignancy. Any decision to reduce the dose will be made following a discussion with the chief investigator.

Upadacitinib has been selected as the exemplar JAK inhibitor of choice for this trial. Upadacitinib is a JAK1 inhibitor, with some JAK2 inhibition, which shows good efficacy in the management of atopic eczema (an IL-4/T2-mediated disease).^19^ Its inhibitory action across both JAK1- and JAK2-mediated pathways provides a strong mechanistic rationale for its use in PPP.^4^ To date, there have been over 50 reported cases indicating the efficacy of upadacitinib in PPP, contributing to a growing clinical interest in its use.^20 21^ The findings of this study will inform the decision regarding drug choice for a future definitive RCT.

### Comparator

Retrospective placebo-controlled data from the APRICOT (National Institute of Health and Social Care Research [NIHR]reference: 13/50/17; Research Ethics Committee [REC] number: 16/LO/0436; International Standard Registered Clinical/soCial sTudy Number [ISRCTN] number: ISCRTN13127147) will be used to generate an indication of effect size for the purpose of estimating the required sample size of a definitive RCT.^16^ Placebo controls in the APRICOT previously received 0.67 mL of vehicle solution daily through self-administered subcutaneous injection over 8 weeks. The IMP in APRICOT was anakinra (Kineret; SOBI, Stockholm, Sweden; 100 mg/0.67 mL daily delivered via self-administered subcutaneous injection).

### Outcomes

#### Primary outcomes

The following outcomes will be assessed after 24 months of recruitment, or when the recruitment target of 20 participants is achieved (whichever occurs first):

Overall proportion of potential participants identified who enrolled in the trial, termed the ‘recruitment rate’.‘Potential participants identified’ is defined as those who have direct contact with the research team.Overall proportion of participants achieving ‘good adherence’ (proportion of days covered >80%) during the trial.‘Proportion of days covered’ is defined as the total medication taken during the 8-week trial period as a proportion of the total medication dispensed.Overall proportion of participants who view JAK inhibitor therapy in PPP to be ‘acceptable’.Acceptability will be measured based on responses to the following question at the end of the 8-week treatment period: ‘Overall, how acceptable was taking upadacitinib to you?’A 5-point Likert scale will be used, with answers dichotomised into acceptable (acceptable/completely acceptable) or unacceptable (completely unacceptable/unacceptable/neutral)

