### Sample size rationale

We will aim to recruit 20 participants, in keeping with other published feasibility studies.^24 25^ Over a 24-month recruitment period, we anticipate approaching a total of around 100 potentially eligible individuals. Based on previous experience, we anticipate that the actual recruitment rate would be no less than 20%, so this would provide us with at least 20 participants.

With 100 approached participants, if 20 (20%) are recruited into the trial, this would allow us to estimate the 95% CI for the recruitment rate with precision of at least ±8%. Assuming 75% of participants adhere to treatment at least 80% of the time (as observed in APRICOT), a sample size of 20 participants would allow us to estimate ≥80% treatment adherence with a 95% CI: 51% to 91%. With 20 participants on treatment, JAKPPPOT will estimate a PPPASI50 in the JAK inhibitor arm with precision of at least ±3.43 PP-PASI points. This is based on figures derived from the APRICOT (mean baseline PP-PASI: 17.8; SD for the PP-PASI change at 8 weeks in active arm: 7.32).^16^ A PPPASI50 is an outcome that has been analysed as a primary/secondary endpoint in several PPP trials and was described as ‘treatment success’ during patient and public involvement (PPI) discussions with people with PPP.^26^ The PP-PASI reduction in the treatment arm will inform the sample size calculation for a larger definitive trial.

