### Progression criteria and rationale

Progression criteria have been outlined to determine whether it is appropriate to progress to a subsequent adequately powered RCT, shown in table 2. Findings from the primary and secondary quantitative outcomes will be incorporated with the qualitative findings to inform decisions regarding an ‘intermediate’ results in any domain (ie, upgrade to feasible or downgrade to non-feasible). All recommendations will be reviewed by the trial steering committee (TSC). For criteria judged to be intermediate or non-feasible, the study team will examine the likely causes and consider whether a mitigation strategy could be successfully implemented.

**Table 2 T2:** Progression criteria for the JAKPPPOT trial

Domain	Non-feasible	Intermediate	Feasible
Recruitment: proportion of potential participants identified who enrolled in the trial	<20%	20–40%	>40%
Adherence: proportion of participants achieving ‘Good’ adherence (>80% of medication taken as prescribed)	<20%	20–80%	>80%
Acceptability: proportion of participants who view JAK inhibitor therapy in PPP to be ‘acceptable’	<20%	20–80%	>80%

JAK, Janus kinase; JAKPPPOT, Janus kinase inhibitors in palmoplantar pustulosis: a mixed-methods feasibility; PPP, palmoplantar pustulosis.

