### Adherence

Adherence will be assessed by counting any remaining medication via inspection of medication packaging at the end of each 4-week period (visit 3 and visit 4) to determine the proportion of days covered (total medication taken/total medication dispensed). If the packaging is unavailable, participants’ responses to the Voils DOSE-Nonadherence measure will be used as a surrogate.^27^

A high adherence rate is expected for several reasons. The tablet is easy to administer, and there is a relatively high burden of clinic visits over the 8-week treatment period. This will remind participants to take the medication and allow any compliance issues to be identified and addressed quickly.

Previous studies have demonstrated an association between an adherence rate of >80% and improved outcomes, when compared with an adherence rate of <80%, in certain disease contexts (eg, following a myocardial infarction).^28 29^ An 80% adherence threshold is often used, therefore, as a key measure of adherence in the context of clinical trials.^30^

The optimal threshold for adherence will differ depending on the specific disease, medication and population in question. Given the paucity of current literature regarding the use of upadacitinib in the management of PPP, it is not currently possible to determine the necessary adherence threshold for this specific context, and so the accepted threshold of >80% adherence rate has been used.^30^ Given the small numbers of trial participants, a wide intermediate progression criteria window has been specified, allowing findings from the integrated qualitative study to be incorporated into the analysis.

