bHCG, beta-human chorionic gonadotropin; BSA, body surface area; CXR, chest X ray; DLQI, Dermatology Life Quality Index; EQ5D-5L, European Quality of Life 5 Dimensions 5 Level Version; Hb, haemoglobin; HBV, Hepatitis B virus; HCV, Hepatitis C virus; IMP, investigational medical product; PPP, palmoplantar pustulosis; PP-PASI, Palmoplantar Pustulosis Psoriasis Area and Severity Index; PPP-IGA, Palmoplantar Pustulosis-Investigator Global Assessment; RCT, randomised controlled trial; TB, tuberculosis.

The treatment period (visits 1–4) is 8 weeks. At the start of the treatment period, eligible patient participants will receive upadacitinib, to be administered daily as an oral tablet for 8 weeks. Participants will receive 4 weeks of medication at Visit 1 (baseline) and Visit 3 (week 4).

The follow-up period (visit 5) at week 12 will be used to assess disease relapse off study treatment, follow-up any adverse events and plan for post-trial management of their condition. Participants will also be asked the following question to scope out their views on a future RCT: ‘Would you be interested in participating in a trial similar to this with either a dummy arm or active comparison drug arm in the future?’. A final safety review (visit 6) will be carried out at week 20 to assess for any further adverse events.

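### Adherence is scored against medication dispensed, so a participant who takes 23 to 28 of the first 28 tablets and is not re-supplied counts as 'good adherence' after 41% to 50% of the planned course

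*Protocol article*

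**What the plan says.** Under Primary outcomes, a participant has good adherence if "proportion of days covered >80%) during the trial". That proportion is "defined as the total medication taken during the 8-week trial period as a proportion of the total medication dispensed". The Adherence section repeats the formula as the operating rule: remaining tablets are counted at Visits 3 and 4 "to determine the proportion of days covered (total medication taken/total medication dispensed").

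The text after Table 3 (Study procedures) says upadacitinib is "to be administered daily as an oral tablet for 8 weeks" and gives the supply schedule: "Participants will receive 4 weeks of medication at Visit 1 (baseline) and Visit 3 (week 4"). Table 3 shows the same two dispensing visits.

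Table 2 (Progression criteria) words the criterion as ">80% of medication taken as prescribed". It calls the domain feasible above 80% of participants, intermediate from 20% to 80%, and non-feasible below 20%. The Sample size rationale describes adherence as a share of time and assumes that 75% of participants reach the 80% level.

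No section sets the denominator at the full 8 weeks or says how to score someone who stops before the second supply. There is a fallback, but only for missing packaging: "If the packaging is unavailable, participants’ responses to the Voils DOSE-Nonadherence measure will be used as a surrogate".

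**The concern.** A measure named for days covered over an 8-week period should fall when days go uncovered. With tablets dispensed as denominator, the second four weeks enter the score only if the second supply is handed out. Someone who finishes or nearly finishes the first supply and then stops is scored on four weeks alone.

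Adherence is one of three primary feasibility domains, and the Background justifies studying it partly by concerns about the acceptability of this drug class. Stopping at about the four-week visit is one way such concerns could show themselves, and the stated rule records it as success. Under Progression criteria, the qualitative findings are used to move an intermediate result up or down. A domain wrongly scored as feasible would not go through that step and would meet only the general review by the trial steering committee.

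**Working it through.** **Inputs.** Planned sample of 20 ("We will aim to recruit 20 participants"); assumed 75% with good adherence (Sample size rationale); threshold above 80% (Primary outcomes); two 4-week supplies and once-daily tablets for 8 weeks (Study procedures).

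**Assumptions.** The article gives weeks, not tablet counts, so I take 28 tablets per supply and 28 + 28 = 56 for the course. I also take it that someone who has stopped is not given the second supply.

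**The plan's own figure.** 75% of 20 is 15. The exact (Clopper-Pearson) 95% interval for 15/20 is 50.9% to 91.3%, which reproduces the stated 51% to 91%. That figure is sound and is not affected by this point.

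**Step 1: score with one supply dispensed.** Stated score = t/28; coverage of the planned course = t/56.

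| Tablets taken (t) | t/28 | Stated rule | t/56 | Planned-course rule |
|---|---|---|---|---|
| 14 | 50.0% | not good | 25.0% | not good |
| 22 | 78.6% | not good | 39.3% | not good |
| 23 | 82.1% | good | 41.1% | not good |
| 25 | 89.3% | good | 44.6% | not good |
| 28 | 100.0% | good | 50.0% | not good |

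The two rules disagree for t = 23 to 28 and nowhere else in the one-supply case. With 56 as denominator, good adherence needs at least 45 tablets (45/56 = 80.4%; 44/56 = 78.6%), which nobody can reach on one supply.

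**Step 2: score with both supplies dispensed.** The denominator is already 56, so the two rules agree.

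**Step 3: direction.** On the stated schedule, the number dispensed never exceeds 56. Hence taken/dispensed is never smaller than taken/56, and the error can only raise the count of good adherers.

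**Step 4: effect on the progression category.** 15/20 = 75% and 16/20 = 80% are intermediate; 17/20 = 85% is feasible.
- True count 16: one misclassified participant gives 17/20, and the category changes.
- True count 15 (the plan's assumption): one gives 16/20, still intermediate; two give 17/20, and the category changes.

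**Step 5: how likely.** The article gives no discontinuation rate. As an illustration only, suppose each of 20 participants has a 10% to 30% chance of stopping, with stops spread evenly over 56 days and full adherence until then. The affected window is 6 days (stopping after day 23 to day 28).
- Expected number affected: 20 × 0.10 × 6/56 = 0.2, to 20 × 0.30 × 6/56 = 0.6.
- Chance of two or more, from a binomial with n = 20 and p = 0.10 × 6/56 = 0.011 to 0.30 × 6/56 = 0.032: about 2% to 13%.

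Stops that cluster around the Visit 3 review would raise these figures.

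**The case against.** **Reach.** A reader might infer that every early stopper is counted as adherent, or that the formula ignores all days after a stop. The document does not support that. The first 28 tablets are in the denominator from the start, so stopping on day 10 scores 10/28 = 36%. Anyone re-supplied at Visit 3 is scored against 56. This objection stands and limits the point to the group in Step 1.

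**Likelihood.** A change of category needs one or two people in a short window and a true count close to the boundary. The document offers no rate to show that this will happen. This stands too: the misclassification is certain for the group described, but its effect on the final decision is only possible.

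**Unstated inputs.** The text says participants will receive both supplies, and on that reading the denominator is always 56. This is fair for those who continue. But the text does not say that someone who has stopped would still be dispensed four more weeks, nor that 56 applies regardless.

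**Contradiction with Table 2.** It is tempting to say that Table 2 contradicts the formula. That goes too far. If treatment is stopped on medical advice, later doses are arguably no longer prescribed, and Table 2's wording can then fit taken/dispensed. What can be said is that the two are not clearly the same, and that the share-of-time wording in the Sample size rationale fits the formula poorly.

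**Choice of construct.** Taking doses while on treatment and persisting for the full course are different things, and a pill count against supply is a recognisable measure of the first. True, but the plan names its measure days covered over the 8-week period, which is the second.

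**Other safeguards.** Acceptability, adverse events, withdrawal reasons and interviews would all bring early stops to light. They would not correct the adherence score, and the questionnaire applies only when packaging is missing. The analysis plan, not shown, may say more, but the article itself states the formula twice.

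**Conclusion.** The point holds in limited form. The definition, given under Primary outcomes and again under Adherence, does not measure what its name says for participants who take 23 to 28 tablets and are not re-supplied. They score 82% to 100% and count as good adherers at 41% to 50% of the planned course. All others are classified correctly. This rests on 28 tablets per supply and on no second supply after a stop.

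The error favours 'feasible' only. It is enough to change the category with one participant at a true 16/20, or two at the assumed 15/20. Severity is moderate: the group is narrow, but the measure is a primary progression criterion and 20 participants leave little room. It does not follow that the adherence result will be wrong, or that the stated confidence interval is.

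**What to change.** For the primary measure, divide tablets taken by the 56 daily doses of the planned 8-week course, for every participant who starts treatment, and count days after a permanent stop as uncovered. Use this one definition under Primary outcomes, Sample size rationale, Table 2 and Adherence. The sample size section says at least 80% and the others say more than 80%. This makes no difference to classification, since 80% of 56 is 44.8 doses, but the wording should match.

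Keep taken/dispensed as a secondary measure, labelled as adherence while on treatment.

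The cost is wording only, because the pill counts are already collected. The one drawback is that stops on medical advice will lower the primary figure, so show them on a separate line next to it. Make the change before outcomes are assessed.
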